### Sample size determination with statistical power calculation

Data will be obtained from 712 families at baseline, with 2 children and up to 2 parents per family (given divorce rates, 1.66 parents per family are estimated). Stratification will be used to over-select female service members and high-risk families such that 456 families will have female military parents and 356 families will be high risk. Power is calculated for three types of analytic samples:

A baseline/cross-sectional analysis sample of 712 families and 1,424 children (2 per family), and 1,182 parents (1.66 per family);A panel analysis sample composed of families who participate at both waves of the study. Based on experience and other military studies [44], 75% retention is projected, resulting in 534 families, 1,068 children, and 887 parents at Wave 2;A repeated measures sample, comprising all observations from both waves. With a 75% family retention rate, the sample will include 1,246 (= 712 + 534) repeated family observations and 2,670 repeated child observations, and 2,216 repeated parent observations. The repeated measures sample will be the priority sample for testing study hypotheses.

Effective sample sizes are calculated for a two-level, mixed-effects model per Snijders [45] using an estimated within-family ICC = 0.30. Power is estimated for a standardized regression coefficient in a model with 5 covariates and alpha = 0.05. Effect sizes detectable at .80 power are listed in Table 1.

**Table 1 pone.0295007.t001:** Detectable effect sizes.

Direct, Moderation, and Mediation Effects (n = cross-sectional / panel / repeated)	Detectible Standardized Beta		
	Cross- sectional	Panel	Repeated Measures
**1. Family level predictors** (n = 712 / 534 / 1246; effective n = 1095 / 822 / 1917)	0.085	0.098	0.064
**2. Child level predictors** (n = 1424 / 1068 / 2492; effective n = 2034 / 1526 / 3560)	0.063	0.072	0.047

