### Model building and estimation

Measurement models will be developed first, per the psychometric analyses. Latent variables will be used when computationally possible. Structural models will be built in stages paralleling study aims, assessing model fit to the data at each stage [112]. Analyses will be conducted using AMOS, Mplus 7 [111], STATA [113], and SAS [114]. Item-missing data will be handled using Full Information Maximum Likelihood (FIML) procedures available within Mplus and STATA [115]^.^ This approach is advantageous, as simulation studies have found it performs superior to listwise deletion and multiple imputation [116]. Sampling weighted estimation that corrects for unequal selection and non-response across strata will be used [107, 117]. In general, an alpha of 0.05 will be used to determine support or lack thereof for hypotheses. However, focus will be on effect size and confidence intervals for the distribution of effects [118].

A mixed-effects modeling approach to the multilevel, nested data structure will be used to explicitly estimate within- and between-family variability [119]. Change in children’s outcomes will be evaluated with two types of models: 1) Three-level mixed-effect models with time nested within child and siblings nested within families, where change is assessed using a predictor variable indicating baseline and follow-up time points, and interactions with the time variable test the effects of predictors on changes in outcomes; and 2) Two-level models with siblings nested in families that include autoregressive effects for each outcome (i.e., control for Time 1 levels), thus controlling for stable levels of each construct and testing effects on residualized change. Both approaches to modeling change provide rigorous inferences about the hypothesized relationships [120]. Models will control for: 1) parents’ age, education, and minority and employment status; 2) family type and size; 3) military branch and paygrade. Sensitivity analyses will be conducted to ensure that these controls do not obscure important findings. Strategies for analyzing each aim are described below.

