#### Analyses for aim 2: To assess the role of parents’ psychological health and family processes in mediating relationships between siblings’ early exposures to parental deployment and later youth adjustment

This aim highlights four indirect pathways through which deployment(s) influence youth adjustment. Deployment factors studied in Aim 1 are expected to be negatively related to parents’ psychological health, parental efficacy, marital relationship quality, and family functioning at Time 1, which in turn will be positively related with youth adjustment at Time 2. The magnitude and statistical significance of the indirect effects of deployment through each of these processes will be tested using the INDIRECT command within Mplus, which employs a product of coefficients method of testing mediation [121] and the bootstrap method to compute standard errors for the significance test [122]. Importantly, the four indirect pathways will be tested concurrently, highlighting not only which pathways are critical for understanding the potential enduring effects of parental deployments on youth adjustment, but also the relationships among them. Differences across siblings also will be assessed.

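### The Aim 2 test of each indirect effect rests on a bootstrap standard error, which ignores the skewness of a product and costs power when both paths are small

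*Protocol article*

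**What the plan says.** The section on analyses for Aim 2 tests indirect effects with the INDIRECT command in Mplus, "which employs a product of coefficients method of testing mediation", and adds "the bootstrap method to compute standard errors for the significance test". The deployment factors and mediators belong to Time 1, and the mediators are the variables "which in turn will be positively related with youth adjustment at Time 2". Four pathways are tested together.

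Under model building and estimation the decision rule is general: "In general, an alpha of 0.05 will be used to determine support or lack thereof for hypotheses". The next sentence says that "focus will be on effect size and confidence intervals for the distribution of effects", without giving the type of interval.

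The power section works with alpha 0.05, "using an estimated within-family ICC = 0.30" and 0.80 power. For the panel sample, Table 1 gives a detectable standardized beta of 0.098 for family-level predictors (effective n 822) and 0.072 for child-level predictors (effective n 1526). The text below the table says these figures also apply to mediation effects, meaning products of path coefficients.

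**The concern.** The Aim 2 sentence gives the bootstrap one task, which is to supply a standard error. A significance test built on a standard error is ordinarily estimate/SE against a symmetric reference. A percentile rule needs no standard error, so the sentence as written does not describe one.

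The sampling distribution of a product of two coefficients is skewed and peaked unless at least one path is large relative to its standard error. Dividing the product by a standard error discards that shape, although the same bootstrap draws contain it. The result is a test whose true error rate lies below 0.05 and whose power is lower than it need be.

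Aim 2 is the mechanism aim, and alpha 0.05 decides whether a hypothesis counts as supported. A real but modest pathway could be reported as unsupported because of the form of the test.

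**Working it through.** **Inputs.** Effective n and detectable betas come from Table 1; alpha, power and ICC from the power section. The panel sample is the relevant one, because Aim 2 puts mediators at Time 1 and outcomes at Time 2. Two-sided alpha is an assumption; it reproduces Table 1.

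**Step 1: reproduce the plan's figures.** Effective n in the panel is 1068/1.3 = 822 (family level) and 1068/0.7 = 1526 (child level). Detectable beta = (1.960 + 0.842)/√(effective n):
- 2.802/√822 = 0.098
- 2.802/√1526 = 0.072

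Both match. All 12 entries of Table 1 have power between 0.80 and 0.81 at the printed beta, for a single path.

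**Step 2: one case by hand.** Take both path estimates equal to 0.098 with s = 1/√822 = 0.0349. Each path has z = 0.098 × √822 = 2.81 (two-sided p about 0.005). The bootstrap variance of the product is approximately a²s² + b²s² + s⁴, so in units of s:

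z of the product = 2.81² / √(2 × 2.81² + 1) = 7.89 / 4.10 = 1.93

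This is below 1.96, so the test on the standard error does not reject. Yet the share of draws with a product at or below zero is about 2 × 0.0025 = 0.005. That is less than 0.025, so the 95% percentile limits exclude zero. The same data give opposite answers.

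**Step 3: simulation.** The two path estimates are drawn as independent normals with SE 1/√(effective n). The test on the standard error uses the variance above; the percentile limits are the 2.5 and 97.5 percentiles of simulated products.

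| Effective n | Paths | Product/SE | Percentile limits |
|---|---|---|---|
| 822 | 0.098, 0.098 | 0.37 | 0.62 |
| 1526 | 0.072, 0.072 | 0.38 | 0.62 |
| 822 | 0.12, 0.12 | 0.70 | 0.86 |
| 822 | 0.098, 0.18 | 0.73 | 0.80 to 0.82 |
| 822 | 0.14, 0.14 | 0.90 | 0.96 |
| 822 | 0.18, 0.18 | over 0.99 | over 0.99 |
| 411 | 0.139, 0.139 | 0.38 | 0.62 |
| 411 | 0.18, 0.18 | 0.79 | 0.91 |

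The two rows with 0.098 and 0.072, and the row with 0.139, are one scenario by construction: each beta is scaled to 80% power for a single path. They are not separate confirmations.

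**Step 4: check with a real bootstrap.** Resampling cases in simulated data sets (400 resamples each) gave 0.39 against 0.63 at n 822 with both paths 0.098, and 0.40 against 0.64 at n 411 with both paths 0.139. The approximation in step 3 is adequate.

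**Step 5: error rate at nominal 0.05, effective n 822.**

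| True paths | Product/SE | Percentile limits |
|---|---|---|
| 0 and 0.098 | 0.008 | 0.036 |
| 0 and 0.18 | 0.029 | 0.050 |
| 0 and 0.32 | 0.043 | 0.053 |
| 0 and 0 | 0.0001 | 0.001 |

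With both paths zero, both methods lie far below 0.05, so conservatism there is not peculiar to the test on the standard error.

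**The case against.** Three objections deserve weight.

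- **No normal test is named.** A reader might infer that the plan prescribes a z test and symmetric intervals. It does not. The reference distribution is not stated, the methods reference is not at hand, and the stated emphasis on confidence intervals leaves their type open. An article may leave the interval type to the full analysis plan. This stands as a limit on certainty. It does not dispose of the point, because the article does state what the bootstrap is for, and that use does not describe percentile limits.
- **The loss is confined to small paths.** A reader might infer that the test is badly conservative throughout. The figures do not support that: at 0.18 or more on both paths in the full panel there is nothing to gain, and the power section quotes betas of 0.18 to 0.32 from earlier research. This stands in part. Those betas describe effects of recent deployment on youth outcomes. They are not estimates of the paths from deployment to mediator or from mediator to outcome, and this study concerns long-term effects. Nothing in the article shows that both component paths reach 0.18. Within risk or sex groups, a loss of about 12 points remains even there.
- **Part of the shortfall has another cause.** Percentile limits reach only about 62% at the Table 1 betas. The gap from there to 80% comes from applying single-path detectable betas to products, not from the test. This stands in full.

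**Conclusion.** The concern holds in a limited form. If the bootstrap standard error is used as the Aim 2 text implies, the test of an indirect effect is conservative when both paths are small. The cost is about 25 points of power at the plan's own panel detectable beta, about 6 points at 0.14 on both paths, and nothing from 0.18 upward in the full panel. At effective n 411 with both paths 0.18 it is about 12 points.

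The figures assume two-sided alpha 0.05, equal effective n for both paths, independent path estimates, one mediator at a time, and no loss from unequal weighting. The plan tests four mediators concurrently and uses weights, so the exact figures will differ.

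A reader might also infer that percentile limits would restore 80% power for mediation at the Table 1 betas. They would not. The claim that Table 1 covers products of paths is a separate matter that needs its own correction.

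**What to change.** Replace the statement about bootstrap standard errors in the Aim 2 analysis section with wording such as: *Indirect effects will be judged by 95% percentile bootstrap confidence limits of the product of coefficients, resampling families; the bootstrap standard error will not be used as the basis of the significance test.* For Aim 3, report the same kind of limits for the conditional indirect effects, unless the cited procedure already does so.

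If percentile limits were intended all along, the change only brings the text into line.

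The cost is one sentence and a different summary of the bootstrap draws already planned; no new data are needed. The statistician should confirm that the chosen software can resample families with the sampling weights, strata and latent variables in the planned models.

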#### Analyses for aim 3: To assess the moderating role of parent and sibling sex, and vulnerability and support in relationship between siblings’ exposures to parental deployment and later youth adjustment

This aim identifies risk and protective factors that may amplify or dampen direct and indirect links between deployments and youth outcomes. Continuous moderators will be tested using procedures outlined by Preacher, Rucker, and Hayes [123]. Specifically, conditional indirect effects will be estimated, with the expectation that relationships between deployment and mediating variables will be stronger when parents experience greater vulnerability and less support, and that relationships between mediating and outcome variables will be stronger when youth experience greater vulnerability and less support. Multi-group analyses will be used to test categorical moderators (i.e., parent and child sex), using likelihood ratio (chi-square) tests to assess whether unconstrained models that allow groups to vary fit better than models constraining direct effects to be equal across groups [105].

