**Simple Effects**			
**3. Family level predictors within risk and sex groups** (n = 356 / 267 / 623; effective n = 548 / 411 / 958)	0.120	0.139	0.091
**4. Child level predictors within risk and groups** (n = 712 / 534 / 1246; effective n = 1017 / 763 / 1780)	0.088	0.102	0.067

Power for tests 1 and 2 in the table apply to direct effects (**Aim 1** paths in Fig 1); mediation effects (products of path coefficients; **Aim 2** paths in Fig 1), and moderating effects (differences in slopes/interactions; **Aim 3** paths in Fig 1); Tests 3 and 4 represent simple slopes for associations within levels of the moderators family risk status and service member sex, which represent the lowest powered tests.

Some cite 0.10 as a “small” effect size for a partial correlation, which is comparable to a standardized beta coefficient [46]. Recent findings about effects of recent deployment (duration, trauma) effects on military youth outcomes gave standardized beta effect estimates in the range of 0.18 to 0.32, on average [44]. These reported effects were controlling for baseline levels in child outcomes and therefore represent effects on residual change, giving confidence that the study is adequately powered. Importantly, power will be further increased through the use of latent variables, which increase measure reliability [47], correlated mediators and outcomes in multivariate analyses [48], and including control variables that explain variance in mediators/outcomes (particularly true in panel analyses). However, power may decrease due to the unequal weighting effect [49].

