#### Analyses for aim 1: To assess direct relationships between the timing, frequency, duration and content of siblings’ early exposures to parental deployments and later youth adjustment

Maladjustment is hypothesized to be greater for children whose exposures began earlier (operationalized as child age at first deployment, including gestational age, coded from archival data), were more frequent (i.e., total number of deployments during the child’s lifetime) prolonged (i.e., total days deployed), ended more recently (i.e., days since end of most recent deployment), or who were exposed to deployments where parents’ experiences were more traumatic (i.e., total scores on self-report Combat Exposure items). These hypotheses will be tested using a SEM framework, where a series of path models will estimate the direct effects of deployment characteristics on each indicator of adjustment. Paths from the independent variables will be tested concurrently, thus establishing the unique association for each deployment risk factor. Interactions between different deployment components—frequency, duration, timing, and content—will also be examined to determine whether long-term effects of deployment are exacerbated or mitigated for various deployment combinations. Within-family comparisons will be conducted to determine whether these direct effects differ across siblings.

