This study will identify downstream consequences of early exposure to parental deployment during a key developmental period and contribute to literature about children’s risk and resilience in the family context. It will generate insights about how military-connected children compare to national samples of children on key outcome variables, taking exposures to adversity into account. It will contribute to understanding the extent to which military-connected children’s outcomes during adolescence are accounted for by characteristics of parental deployments they experienced early in life vs. their own and their parents’ early exposures to other adverse experiences. It will reveal within-family variations in military children’s outcomes and their antecedants. It will identify which risk and resilience processes appear to be most important for particular adolescent outcomes among children exposed early in life to parental military deployments, and how these effects differ as a function of parent and child assigned sex.

The implications will be important for prevention programs in DoD, schools, health care providers, and community organizations as they consider how best to optimize long-term outcomes for children.

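### The stated test for moderation by sex covers only direct effects, so differences by sex in the mediating pathways, which the article says it will report, have no stated test

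*Protocol article*

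**What the plan says.** All references are to the protocol article.

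- **Scope.** The section on analyses for Aim 3, whose heading names parent and sibling sex first, says the aim concerns "risk and protective factors that may amplify or dampen direct and indirect links between deployments and youth outcomes".
- **Continuous moderators.** In the same section, "conditional indirect effects will be estimated, with the expectation that relationships between deployment and mediating variables will be stronger" under greater parental vulnerability and less support. A parallel expectation follows for the mediator-to-outcome leg, so both legs are covered.
- **Sex.** "Multi-group analyses will be used to test categorical moderators (i.e., parent and child sex), using likelihood ratio (chi-square) tests" of whether unconstrained models "fit better than models constraining direct effects to be equal across groups". No other test for sex is stated.
- **Use of the term.** Under Aim 1, "a series of path models will estimate the direct effects of deployment characteristics on each indicator of adjustment". The Aim 2 section keeps the term indirect effects for paths through the four mediating processes. The text below Table 1 likewise separates direct effects (Aim 1 paths) from "mediation effects (products of path coefficients", which it assigns to the Aim 2 paths.
- **Planned conclusion.** The Innovation section says the study will identify which processes matter most for particular adolescent outcomes, and "how these effects differ as a function of parent and child assigned sex".
- **Narrower wording.** The section on the model for the study and the statement of Aim 3 in the introduction describe sex only as a moderator of the relationship between deployment exposure and youth outcomes.

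**The concern.** A likelihood ratio test responds only to the parameters that its constrained model fixes. If only the deployment-to-outcome paths are held equal, the deployment-to-mediator and mediator-to-outcome paths are free in both models, and a difference by sex in them adds nothing to the chi-square. The promised statement on how processes differ by sex is a claim of moderated mediation, and no stated test supports it.

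Comparing mothers' and fathers' deployments is a stated reason for including enough female service members. If their deployments differ mainly through parents' psychological health or parenting, a non-significant result from the stated test would say nothing about that difference, yet it could be read as evidence of similarity.

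**Working it through.** **1. The plan's own figures.** Table 1 reproduces. For family-level predictors, effective n = 1,424 / (1 + 0.30) = 1,095, and detectable beta = (1.960 + 0.842) / √1,095 = 0.085, as stated. For child-level predictors, 1,424 / (1 − 0.30) = 2,034, and 2.802 / √2,034 = 0.062, against 0.063 stated. The article applies these rows to direct, mediation and moderation effects alike. It gives no figure for the multi-group test by sex.

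**2. What the test compares.** Write *a* for deployment to mediator, *b* for mediator to outcome, and *c* for deployment to outcome given the mediator.

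| Quantity | Equal across sexes in the constrained model? | Can a sex difference here alone raise the chi-square? |
|---|---|---|
| *c* | yes | yes |
| *a* | no | no |
| *b* | no | no |
| *a·b* (indirect effect) | no | no |

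This follows from the constraint and needs no simulation. If *c* is equal, the rejection rate is alpha, however far *a* or *b* differ.

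**3. Illustration.** Inputs from the article: 456 families with a female military parent, so 712 − 456 = 256 with a male one; alpha 0.05, taken as two-sided; 75% retention, giving 342 and 192. Assumed: standardised variables, *c* = 0.10 in both groups, *b* = 0.30 unless varied, and the *a* values shown. The upper value 0.32 is borrowed from the article's range for deployment effects on youth outcomes, not on mediators.

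Test of *a*, 0.32 against 0.10:
- SE = √[(1 − 0.32²)/456 + (1 − 0.10²)/256] = √(0.00197 + 0.00387) = 0.0764
- z = 0.22 / 0.0764 = 2.88; power = Φ(2.88 − 1.96) = 0.82

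Simulated rejection rates (2,000 replicates; two-group path model; Wald tests, delta method for *a·b*):

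| Mothers vs fathers | Stated test (*c* only) | Test of the differing path | Test of the *a·b* difference |
|---|---|---|---|
| *a* 0.32 vs 0.10 | 5% | 83% | 66% |
| *a* 0.32 vs 0 | 5% | 98% | 94% |
| *b* 0.35 vs 0.05 | 5% | 97% | 89% |
| *a* 0.32 vs 0.10, panel size | 5% | 69% | 52% |

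A repeat run agreed within simulation error. A separate run with likelihood ratio tests and paths of 0.4 vs 0.1 gave 4–6% when only *c* was constrained, and 91–99.8% when *a*, *b* and *c* were all constrained. When only *c* differed, the stated test rejected 94%, so it works for what it targets.

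**4. If the mediators are left out.** The path tested is then the total effect, *c* + *a·b*.
- *a* 0.32 vs 0.10: mothers 0.10 + 0.32 × 0.30 = 0.196; fathers 0.10 + 0.10 × 0.30 = 0.130; difference 0.066.
- SE = √[(1 − 0.196²)/456 + (1 − 0.130²)/256] = 0.0771; z = 0.86; two-sided power about 14%.

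Simulation across these scenarios gave 11–23%. The difference does register, but weakly, and it cannot be assigned to a pathway.

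**The case against.** Four counter-arguments carry weight.

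- **The sex hypothesis may be narrower.** Where the introduction names sex, it speaks only of exposure and outcome. It names intervening variables for adversity and support, not for sex. On that reading the test fits its hypothesis, and only the Innovation sentence goes too far. This stands in part. But the Aim 3 analysis section lists sex in its heading and then sets the scope as direct and indirect links, so the scope has to be reconciled either way.
- **Direct effects can mean any single-arrow path.** In general structural equation usage this is true, and the mediator legs would then be constrained too. The article's own usage points the other way, and the Aim 3 section sets direct against indirect a few lines earlier. If the authors meant all structural paths, the same short edit settles it.
- **Sex-specific estimates would still exist.** The unconstrained model yields every path by sex, the text below Table 1 foresees simple slopes within service member sex, and the modelling section puts the focus on effect sizes and confidence intervals. A reader might infer that a mediated difference would necessarily be reported as no moderation by sex. The article does not support that: the difference could be described, though no stated procedure compares it between groups.
- **The order of constraints is often left to an analysis plan.** That would excuse silence. Here the article does name the constrained parameters, and as named they are narrower than the stated scope.

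**Conclusion.** The point holds as a mismatch between the stated test and the stated scope. Followed as written, and with direct effects read as the article uses the term, the test for sex does not address differences in the mediating pathways. In a model with mediators, its chance of rejecting on such a difference alone is alpha. In a model without them, it tests the total effect.

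A reader might infer that the study cannot detect mediated sex differences at all, or take the gap between 5% and 83% as power lost in this study. Neither follows. The 5% is the nominal level, because the direct paths were set equal. The other rates rest on assumed path values and on a simple model without siblings, weights or latent variables. They also group by parent sex only, because the article gives no counts by child sex. None of these simplifications lets a constraint on *c* test *a* or *b*. The change is worth making before analysis but does not affect the design or the data collected.

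**What to change.** In the analyses for Aim 3, state that for parent sex and for youth sex, in addition to the direct-effect constraint:

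1. deployment-to-mediator paths are constrained equal across groups in one nested model;
2. mediator-to-outcome paths are constrained equal in another;
3. the between-group difference in each of the four indirect effects is reported with a bootstrap 95% confidence interval, in keeping with the bootstrap already planned for Aim 2.

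Say whether the direct-effect comparison is made with the mediators in the model, and align the sex hypothesis in the introduction with the scope in the analysis section. If the authors intend only the narrower hypothesis, limit the Innovation sentence on sex to direct effects.

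No new data are needed. The cost is more tests within Aim 3: four indirect effects by two sex moderators gives eight differences for each deployment characteristic and outcome. Wide intervals for some of these should be expected and reported as such.
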